## Recruitment

*Item 15: Strategies for achieving adequate participant enrolment to reach target sample size.*

Patients will be recruited mainly via inpatient psychiatric departments, family practices, general practitioners and psychiatric and psychotherapeutic outpatient units. The project will be conducted in collaboration with two health insurances, the AOK Baden-Württemberg (AOK) and the Techniker Krankenkasse (TK), who will support the recruitment with a targeted approach of general practitioners, psychiatrists and psychotherapists. All hospitals, clinics and practices will receive information material, such as flyers and posters, to inform their patients about the project. In addition, AOK and TK will publish articles in media distributed for their members during the course of the project. The TK further will inform eligible patients directly via phone calls. Recruitment will be additionally performed via social media posts (Instagram and Facebook), newsletters of professional associations, email distribution lists of universities, local influencers and regional newspapers and television.

Interested patients will first attend a preliminary telephone screening of eligibility criteria and will receive general information about the project (see also fig. 2). Patients will be screened for somatic contraindications for exercise via the Physical Activity Readiness Questionnaire (PARQ) (Thomas et al., 1992) and will be informed that they have to provide a physician referral for ImPuls before pre-assessment. In case of any suspicion of somatic contraindications, that might oppose participation (e.g., heart diseases or orthopedic problems), patients will be asked to provide an additional medical consult from their general practitioner or a medical specialist. Eligible participants will be invited for a first inhouse meeting taking place in a study site close to their residence. Within the meeting, they will provide informed consent for study participation, receive information about the study site and will be screened initially for symptomatology related to the exclusion criteria to prepare for the structural diagnostic interview. The telephone screening and initial interview will be performed by trained research assistants. Following this first inhouse meeting, psychologists with a M.Sc. degree undergoing a training in cognitive-behavior therapy, who will be trained by an external expert for structured clinical interviews, will conduct the structured clinical interview for DSM-5 (SKID-5-CV) (Beesdo-Baum et al., 2019) to confirm eligibility.

Once six patients at the same site will be found to be eligible for participation, they will receive online questionnaires via the web-based data management system REDCap (Harris et al., 2019; Harris et al., 2009) and a accelerometer-based Physical Activity sensors (MOVE 4; movisens GmbH) which will be worn for seven consecutive days (pre-assessment). Online questionnaires and the assessment of physical activity will be carried out within a period of 14 days. On Day 15, the six patients will be randomized as a group to either the intervention or control condition. In case of an assignment into the intervention condition, study sites will have to start the intervention within 14 days. Before the start of the intervention, global symptom as well as disorder-specific symptom severity will be assessed again to check whether participants meet the cut-off criteria for a mental disorder. In each study site, 60 patients are planned to be recruited and randomized, resulting in 10 allocations per site. The intervention group will complete the exercise intervention in addition to TAU, while the control group will receive TAU within the real-world outpatient mental health care setting in Germany. The TAU condition is intended to represent the typical treatment patients receive in the German outpatient health care system. The procedure of the pre-assessment phase will be repeated six months (Post) and 12 months (Follow-up) after randomization. After the completion of all assessments, patients of the control group will receive 450€ as reimbursement for their time.

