   3. To what extent do patients’ integration of motivational/volitional core components of the ImPuls intervention (e.g., barrier management, goal-setting, phone contacts) as well as changes in respective individual behavioral determinants (e.g., action and coping plans; physical activity-related health competencies) mediate its effect on their exercise adherence?
   4. To what extent do changes in patients' transdiagnostic psychological processes (e.g., emotional regulation, repetitive negative thinking or perceived stress) mediate the treatment effects?

*Item 8: Description of trial design including type of trial (e.g., parallel group, crossover, factorial, single group), allocation ratio, and framework (e.g., superiority, equivalence, non-inferiority, exploratory).*

The study will be led by researchers based at the University of Tuebingen in Germany, and will be conducted in 10 different study sites across Baden-Württemberg, a region in South-West Germany. The entire project will be conducted between September 2020 and February 2024. The study has been registered at the German Clinical Trial Register (ID: DRKS00024152, 05/02/2021) and has been approved by the local ethics committee for medical research at the University of Tuebingen (ID: 888/2020B01, 02/11/2020). A pragmatic multi-site block-randomized controlled trial with two treatment arms (ImPuls + TAU vs. TAU) and three points of assessment (pre, post, follow-up) will be conducted (see fig. 1). All outcomes will be included at all assessments. Study completion and reporting will be carried out in accordance with the Consolidated Standards of Reporting Trials (CONSORT) [52], the Template for Intervention Description and Replication (TIDieR) (Hoffmann et al., 2016) and the Consensus on Exercise Reporting Template (CERT) (Slade et al., 2016).

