# Interventions

*Item 11a: Interventions for each group with sufficient detail to allow replication, including how and when they will be administered.*

**ImPuls.** The exercise intervention “ImPuls” (Wolf et al., 2020) will be delivered to groups consisting of 6 patients and will be divided into a supervised and partially-supervised period. BCTs, such as goal setting, self-monitoring, formation of concrete exercise plans and coping planning, will be integrated to promote sustained exercise behaviour change (Abraham et al., 2009; Geidl et al., 2012; Michie et al., 2011). The intervention structure and contents are displayed in Figure 3 and Table 1. Participants will receive ImPuls in addition to TAU.

***Supervised Period (weeks 0-4).*** Patients will participate in a combination of supervised MVAE sessions and group sessions with educative elements integrating BCTs (see table 1) in groups with a total duration of 120 minutes each session. Supervised MVAE will be provided twice a week and will consist of either running or fast walking. MVAE will last 30 minutes and participants can choose between a standardized interval-based or endurance method protocol. Both training methods will be conducted with at least moderate intensity, which is tracked by a heart rate monitor (SIGMA iD.FREE) combined with a chest strap (SIGMA R1 Bluetooth Duo Comfortex+) and the Borg Rating of Perceived Exertion (RPE) Scale (Borg, 1982). Moderate to vigorous intensity is defined as at least 64 % of maximum heart rate, subtracting age from 220 (Garber et al., 2011) and at least 13 points of the RPE Scale (Borg, 1982). The ImPuls smartphone application (“ImPuls-App”) developed specifically for ImPuls supports the participants and therapists during MVAE. In weeks 2, 3 and 4 patients will engage in additional 30-minutes MVAE, which is chosen based on their own interests and preferences. Therapists provide a list of MVAE highlights in each study site (i.e. offers in local sport clubs, yoga studio, gyms) which can be found and selected in the “ImPuls-App”.

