### Implementation

*Item 16c: Who will generate the allocation sequence, who will enrol participants, and who will assign participants to interventions.*

The randomization sequence is generated independently of the study coordinator and the research team responsible for data collection and management. The sequence is generated using a varying-size permuted block design, stratified by study site. This procedure ensures an appropriate balance in the number of treatment and control groups per study site. Randomization codes are generated digitally and concealed on a secure system. The group-allocation sequence is concealed from the research team responsible for data collection and management until the planned unblinding.

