## Statistical Methods

*Item 20a: Statistical methods for analyzing primary and secondary outcomes. Reference to where other details of the statistical analysis plan can be found, if not in the protocol.*

*Item 20b: Methods for any additional analyses (e.g., subgroup and adjusted analyses).*

*Item 20c: Definition of analysis population relating to protocol non-adherence (e.g., as randomised analysis), and any statistical methods to handle missing data (e.g., multiple imputation).*

To test Hypotheses 1, 2, 3a and 4 we will use multilevel modeling to establish the treatment effects on the primary outcome (global symptom severity) and the secondary outcomes (major depressive disorders, insomnia, panic disorder, agoraphobia, PTSD, QALYs, exercise). In these analyses, each outcome will be predicted by the group (ImPuls + TAU vs. TAU), time (pre vs. post vs. follow-up), and their interaction. Given that the randomization is stratified by study site, we will account for the effects of study site in all analyses. All analyses will be performed on intention-to-treatment basis, using maximum likelihood estimations.

To test Hypothesis 3b, mediation analyses will be performed to test the indirect effects of the treatment on the primary outcome that are mediated by the changes in the putative mediators (self-reported exercise in minutes per week, accelerometry-based moderate to vigorous physical activity (MVPA); from pre to post, pre to follow-up and post to follow-up). We will compute standardized change scores for the outcome and mediators (Lee et al., 2019). In a path model (specified in the framework of structural equation modeling), the group variable predicts the changes in the mediators, and these mediating factors further predict the change score in the outcome. The indirect effects are defined by the products of the group-mediator and mediator-outcome effects. As exploratory analyses, we will also examine other forms of mediations proposed by Goldsmith et al. (Goldsmith et al., 2018), encompassing cross-lagged effects and latent change score models. As recommended by Usami et al.(Usami et al., 2019), we will first test whether these models fit the data well (and which model fits the data best), and then investigate the indirect effects of the treatment on the outcome.

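### Patients are randomised in intact groups of six, but the analysis accounts only for site, so any correlation within groups makes standard errors too small and breaks the 5% error rate

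*Protocol*

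**What the plan says.** **Unit of randomisation.** Recruitment (Item 15) waits until six patients at one site are eligible, runs the pre-assessment, and then: "On Day 15, the six patients will be randomized as a group to either the intervention or control condition". The same section adds: "In each study site, 60 patients are planned to be recruited and randomized, resulting in 10 allocations per site". Item 8, in the Introduction, says the trial "will be conducted in 10 different study sites across Baden-Württemberg". Implementation (Item 16c) describes permuted blocks of varying size, stratified by site, and confirms that groups are what is allocated: "This procedure ensures an appropriate balance in the number of treatment and control groups per study site".

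**Delivery.** Under Interventions (Item 11a), ImPuls "will be delivered to groups consisting of 6 patients".

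**Analysis.** Statistical Methods (Items 20a–c) specifies multilevel modelling in which "each outcome will be predicted by the group (ImPuls + TAU vs. TAU), time (pre vs. post vs. follow-up), and their interaction". In that sentence, group means the arm, not the set of six. The one design feature the section undertakes to handle is the stratification factor: "Given that the randomization is stratified by study site, we will account for the effects of study site in all analyses". The randomised set of six is not mentioned.

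**Sample size.** Item 14 uses a two-sided t-test with d = 0.348, alpha 0.05, 80% power, equal arms and 30% dropout, giving N = 375. It states no ICC and no design effect. The increase to 600 is attributed to the process evaluation.

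**The concern.** Randomising intact groups makes the trial cluster-randomised within site, whatever it is called. The arm comparison is then a comparison of groups with groups, and its error contains the variation between groups in the same site. The planned model has no place for that variation. It treats about 600 patients as independently allocated when there are about 100 allocated units.

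Site does not stand in for the group. Both arms occur in every site, so site terms remove differences between sites. Arm varies only between groups within a site, so group-to-group differences pass straight into the arm contrast.

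The correlation has obvious sources in the ImPuls arm. Patients share sessions and a therapist, may exercise together without supervision in weeks 5–24, and may have their whole group discontinued if more than half drop out (Item 11b). At stake are the confidence intervals and p-values for Hypotheses 1 to 4, including the primary efficacy claim.

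**Working it through.** **1. Reproduce the plan's own figure.** An exact noncentral t calculation with d = 0.348, two-sided alpha 0.05 and 80% power gives 131 per arm, or 262. Then 262 / (1 − 0.30) = 374.3, rounded up to 375. The stated N is therefore exactly that of an individually randomised trial with a design effect of 1.

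**2. Count the randomised units.** 60 patients per site / 6 = 10 groups per site; 10 sites × 10 = 100 groups, about 50 per arm.

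**3. Error rate when the group is ignored.** With m analysed per group, the design effect is DE = 1 + (m − 1) × ICC. The reported standard error is 1/√DE of its true value, and the true two-sided error rate at a nominal 5% is 2 × [1 − Φ(1.96/√DE)]. If only the ImPuls arm is clustered, DE is replaced by the average (DE + 1)/2. The ICC values are assumptions. The value of m is 6, or 6 × 0.70 = 4.2 after the protocol's 30% dropout.

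| ICC | DE, m = 6 | SE ratio, m = 6 | Alpha, m = 6, both arms | Alpha, m = 6, ImPuls only | Alpha, m = 4.2, both arms | Alpha, m = 4.2, ImPuls only |
|---|---|---|---|---|---|---|
| 0.01 | 1.05 | 0.976 | 5.6% | 5.3% | 5.4% | 5.2% |
| 0.02 | 1.10 | 0.953 | 6.2% | 5.6% | 5.7% | 5.4% |
| 0.05 | 1.25 | 0.894 | 8.0% | 6.5% | 6.9% | 5.9% |
| 0.10 | 1.50 | 0.816 | 11.0% | 8.0% | 8.8% | 6.9% |

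Example: at m = 6 and ICC 0.05, DE = 1 + 5 × 0.05 = 1.25, 1.96/√1.25 = 1.753, and 2 × [1 − Φ(1.753)] = 8.0%.

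**4. Does adjusting for site remove the inflation?** This was simulated with 10 sites × 10 groups × 6 patients, five groups per arm in each site, site effects in the model and 20,000 runs per setting.

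- Clustering in both arms: 5.1%, 5.4%, 6.2%, 7.7% and 10.9% at ICC 0, 0.01, 0.02, 0.05 and 0.10.
- Clustering in the ImPuls arm only: 5.5%, 5.7%, 6.4% and 8.0% at ICC 0.01 to 0.10.
- The same data analysed with the randomised group as the unit within site: 4.8–5.1% in every setting.

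Site adjustment does not help, and analysing by group does.

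**5. Random dropout.** Simulations with site effects and 30% random dropout gave 7.1–7.2% at ICC 0.05 and 9.2–9.6% at ICC 0.10 with both arms clustered, and 6.6–7.1% at ICC 0.10 with ImPuls-only clustering. The both-arms results lie slightly above the m = 4.2 column because dropout also makes group sizes unequal. The effective size is 4.2 + (6 × 0.7 × 0.3)/4.2 = 4.5, and the formula with m = 4.5 gives 7.1% and 9.2%.

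**6. Consequence for sample size and power.** Multiplying 262 by DE at m = 6 and dividing by 0.7 gives 412, 468 and 562 for ICC 0.02, 0.05 and 0.10, instead of 375. At the target of 600 (420 completers), power for d = 0.348 with a correct analysis at m = 6 is 93%, 89% and 83%, and stays at or above 80% up to an ICC of about 0.12.

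**The case against.** The strongest reply is that multilevel modelling can include a level for the set of six. The protocol does not list its random effects, and such detail is often left to a statistical analysis plan, which is not available here. The sentence about site does not say that site is the only feature handled. It remains possible that the final model is correct. But the section does more than stay silent: it names the design feature to be handled, gives the reason, and chooses the stratification factor rather than the unit of randomisation. The sample size makes the same individual-level assumption. Repeated measures within patients and site are enough to explain the word multilevel.

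Three further points stand as limits on size:

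- The inflation needs a positive within-group correlation, and none is documented. At ICC 0 there is no problem.
- The correlation that matters is that of change. A stable difference between groups already present at pre largely cancels from the arm-by-time contrast.
- TAU patients in a set share only a site and an enrolment period, so the ImPuls-only columns may be nearer the truth. With 4.2 analysed per group those are 5.4%, 5.9% and 6.9% at ICC 0.02, 0.05 and 0.10, a modest excess.

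It is also true that power at 600 is not threatened, and that with about 100 groups the choice of degrees of freedom matters far less than including the group at all.

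**Conclusion.** The concern holds. The protocol allocates about 100 groups of six, and neither its analysis nor its sample size recognises them. Over assumed ICCs of 0.02 to 0.10 for change, the true two-sided error rate is about 5.4% to 8.8% with 4.2 analysed per group (ImPuls-only clustering at the low end, both arms at the high end), and up to 11.0% with all six analysed and both arms clustered. Confidence intervals are too narrow in the same proportion as the standard errors. The exact size cannot be known from the protocol. Validity of the primary test should not rest on an unstated assumption of zero correlation when one arm is treated in groups. The damage is to the error rate and interval coverage rather than to power at N = 600. This should be corrected before analysis, because it affects the primary and every secondary contrast.

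**What to change.** In Statistical Methods (Items 20a–c):

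- Define the randomised group, use a name for it that cannot be confused with arm, and enter it as a random effect nested in site in every model for Hypotheses 1 to 4. Include its effect at post and follow-up (group-by-time), because a constant group intercept alone largely cancels from the arm-by-time contrast. This is the essential change.
- Preferably allow the group variance to differ between ImPuls and TAU, and test arm contrasts with degrees of freedom reflecting the number of groups (Kenward-Roger or Satterthwaite).
- Apply the same clustering in the mediation models for Hypothesis 3b, for example with cluster-robust standard errors.

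In Sample Size (Item 14), state an assumed ICC and show that 600 still gives adequate power, as it does up to an ICC of about 0.12 under the protocol's own assumptions.

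The cost is protocol or analysis-plan wording, a group identifier in the analysis file, and somewhat wider confidence intervals. No change to recruitment is needed.

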## Allocation

### Sequence Generation

*Item 16a: Method of generating the allocation sequence (e.g., computer-generated random numbers), and list of any factors for stratification. To reduce predictability of a random sequence, details of any planned restriction (e.g., blocking) should be provided in a separate document that is unavailable to those who enrol participants or assign interventions.*

### Concealment Mechanism

*Item 16b: Mechanism of implementing the allocation sequence (e.g., central telephone; sequentially numbered, opaque, sealed envelopes), describing any steps to conceal the sequence until interventions are assigned.*

### Implementation

*Item 16c: Who will generate the allocation sequence, who will enrol participants, and who will assign participants to interventions.*

The randomization sequence is generated independently of the study coordinator and the research team responsible for data collection and management. The sequence is generated using a varying-size permuted block design, stratified by study site. This procedure ensures an appropriate balance in the number of treatment and control groups per study site. Randomization codes are generated digitally and concealed on a secure system. The group-allocation sequence is concealed from the research team responsible for data collection and management until the planned unblinding.

## Blinding (Masking)

*Item 17a: Who will be blinded after assignment to interventions (e.g., trial participants, care providers, outcome assessors, data analysts), and how.*

*Item 17b: If blinded, circumstances under which unblinding is permissible, and procedure for revealing a participant’s allocated intervention during the trial.*

Patients are not blind to allocation. No assessors need to be blinded since primary and secondary outcomes are not based on clinician/diagnostician ratings. The sponsor and his research team responsible for data collection and management and any personal in contact with patients is blinded regarding the randomization procedure. The data analyst is blinded regarding the allocation. He receives the final dataset, which is masked for the treatment condition (the “condition” variable only informs Condition A or B but no real labels of the treatment and control conditions). An unblinded data manager handles the raw data when exporting the data from REDCap.

## Data Collection Methods

*Item 18a: Plans for assessment and collection of outcome, baseline, and other trial data, including any related processes to promote data quality (e.g., duplicate measurements, training of assessors) and a description of study instruments (e.g., questionnaires, laboratory tests) along with their reliability and validity, if known. Reference to where data collection forms can be found, if not in the protocol.*

Please refer to *item 11 d* **“Outcomes”**

*Item 18b: Plans to promote participant retention and complete follow-up, including list of any outcome data to be collected for participants who discontinue or deviate from intervention protocols.*

In accordance with the Evaluation Concept and Record of Processing Activities, all data for evaluation runs through REDCap on a secured LMU internal server providing a stable and traceable coding, storage and security structure as well as data quality measures such as automatic survey reminders, alerts to researchers for telephone reminders to participants, and data type and range checks where appropriate. Missing values on surveys have to be confirmed by participants to be intentional before being able to proceed to the next questionnaire.

The process evaluation data collected via app are stored pseudonymously on a server of the Central Office of the University of Tuebingen (Tue-CO) and transmitted pseudonymously to LMU-Psy. Likewise, videos of the group sessions will be recorded by Tue-MA as part of the process evaluation. These videos will be stored on a hard-drive at the Tü-CO and transferred to the LMU-Psy via RedCap. The routine data of the health insurances (AOK/TK) include outpatient, inpatient, as well as medicines, remedies and aids six months prior and up until six months after completion of the intervention period and are transmitted to the trust center (TUM-TC) on the basis of a pseudonym assigned by the Tue-CO, which is not known to the patients, and from there double pseudonymized to the TU Munich (TUM-HSM). The data stored at LMU-Psy (primary and secondary endpoints, data on progression diagnostics and process evaluation) are transmitted to TUM-TC via a secure connection. From there, they are transmitted to TUM-HSM with the routine data and will be double pseudonymized.

